## Abstract

**Background:**

Asthma is a difficult diagnosis to establish in preschool children. A few years ago, our group presented a prediction rule for young children at risk for asthma in general practice. Before this prediction rule can safely be used in practice, cross-validation is required. In addition, general practitioners face many therapeutic management decisions in children at risk for asthma. The objectives of the study are: (1) identification of predictors for asthma in preschool children at risk for asthma with the aim of cross-validating an earlier derived prediction rule; (2) compare the effects of different treatment strategies in preschool children.

**Design:**

In this prospective cohort study one to five year old children at risk of developing asthma were selected from general practices. At risk was defined as 'visited the general practitioner with recurrent coughing (≥ 2 visits), wheezing (≥ 1) or shortness of breath (≥ 1) in the previous 12 months'. All children in this prospective cohort study will be followed until the age of six. For our prediction rule, demographic data, data with respect to clinical history and additional tests (specific immunoglobulin E (IgE), fractional exhaled nitric oxide (FENO), peak expiratory flow (PEF)) are collected. History of airway specific medication use, symptom severity and health-related quality of life (QoL) are collected to estimate the effect of different treatment intensities (as expressed in GINA levels) using recently developed statistical techniques. In total, 1,938 children at risk of asthma were selected from general practice and 771 children (40%) were enrolled. At the time of writing, follow-up for all 5-year olds and the majority of the 4-year olds is complete. The total and specific IgE measurements at baseline were carried out by 87% of the children. Response rates to the repeated questionnaires varied from 93% at baseline to 73% after 18 months follow-up; 89% and 87% performed PEF and FENO measurements, respectively.

**Discussion:**

In this study a prediction rule for asthma in young children, to be used in (general) practice, will be cross-validated. Our study will also provide more insight in the effect of treatment of asthma in preschool children.

## Background

Asthma is the most prevalent chronic illness in children. It is an inflammatory disorder of the airways and is strongly associated with airway hyperresponsiveness and symptoms like wheezing, shortness of breath, and coughing [1,2]. Potential predictors for asthma in childhood or later in life have been studied widely. Predictors that have already been identified include environmental factors; i.e. exposure to allergens [3-6], tobacco smoke [7,8] , respiratory (viral) infections [9-11], and diet (particularly breastfeeding) [12]. But also 'non environmental' factors such as sex [13,14] and obesity [15,16] are predictors for asthma. It is thought that early identification of children at high risk for asthma may improve their management resulting in fewer respiratory symptoms, exacerbations and emergency medical visits while improving their quality of life (QoL) and preventing loss of lung function and airway remodelling over time [17-20].

A few studies have derived prediction rules to predict asthma later in life [21-23]. Perhaps the most well known prediction rule (clinical asthma-risk index) was developed in the Tucson Children's Respiratory Study by Castro-Rodriguez et al. [22]. This prediction rule was constructed in preschool children from the general population with symptoms of frequent wheezing. Although this prediction rule is helpful to identify children at high risk of (developing) asthma later in life in the general population, it cannot automatically be used in general practice. Factors that determine which children will visit the general practitioner (GP) are not incorporated in the Tucson prediction rule, influencing the strength of the components in the rule. Also a diagnosis of asthma later in life was based on surveys which is a less objective measure compared to a clinical outcome based on spirometry and hyperresponsiveness.

Therefore, Eysink et al. [23] presented a prediction rule for general practice with factors that determine which children will visit the GP. This prediction rule also used an objective outcome measure of asthma at age six; i.e. a combination of current symptoms (complaints of wheezing and/or shortness of breath and/or recurrent coughing) and/or use of β_2 _agonists and/or inhaled corticosteroids during the previous 12 months in combination with airway hyperresponsiveness to methacholine (PC_20 _FEV_1 _≤ 8.0 mg/ml, or > 10% increase in FEV_1 _after rapid acting β_2 _agonists (salbutamol) inhalation if baseline airflow obstruction precluded the methacholine challenge). The Eysink prediction rule was based on age at presentation, wheezing, family history of allergy for pollen, and specific immunoglobulin E (IgE) to house dust mite, cat and dog dander. Although the asthma probability varied from 1.3% to 94.5% with a bootstrapped area under the curve (AUC) between 0.78 to 0.92, it is essential that the rule is validated prospectively on a separate population before use in practice [24]. Clinical prediction rules typically demonstrate reduced performance in a new patient population because they are optimally modeled to the original data set. In the present study Eysink's existing prediction rule will be cross-validated.

Although prediction of asthma in preschool children is important with a view to prevention, the GP also faces therapeutic management decisions in these children at risk of developing asthma. Currently, treatment intensity is categorized according to the international Global Initiative for Asthma guidelines (GINA) [25]. However, according to GINA, available literature on treatment of asthma in preschool children precludes detailed treatment recommendations. Moreover, randomized trials (RCTs) in these young children in primary care are not forthcoming. Therefore, we will determine the effect of different treatment intensities (GINA levels) on symptoms and QoL in preschool children at risk for asthma in a prospective cohort setting. In our population-based prospective cohort study, we will compare the effects of no treatment and the different GINA treatment intensity levels most commonly used by Dutch GPs. The prescription histories will shed an indirect light on treatment adherence (frequency of repeat prescriptions), but the main strength of our approach is that we learn about real-life effects of what physicians prescribe/advise, incorporating real-life adherence levels.

The AiRway Complaints and Asthma DEvelopment (ARCADE) prospective cohort study has two main objectives. First, we will cross-validate the prediction rule of Eysink et al. Second, the effect of different treatment strategies on symptoms and QoL in preschool children will be compared.

This article reviews the study design and baseline data of the children in this general practice based study.

## Methods and design

The ARCADE study is an ongoing multicenter, prospective cohort study which started in 2004 and will end in 2011, when all enrolled children have reached the age of six years. Additional file 1 shows the time frame of the study, including details of the type of contacts with the study population in the various phases of the study. The study was approved by the Central Committee on Research Involving Human Subjects (CCMO/P04.0098C).

### Enrollment of children and time frame

In three areas in The Netherlands, one to five year old children at risk to develop asthma were selected from 14 general practices. Children at risk for asthma were defined as 'visited the general practitioner with recurrent coughing (≥ 2 visits), wheezing (≥ 1) or shortness of breath (≥ 1) in the previous 12 months'.

Figure 1 shows the flow of patients through the study. Briefly, Parents of eligible children received mailed information (including a reply card) about the study from their GP (stage 1). On the reply card the parent(s) could indicate whether they considered participation in ARCADE. A reminder letter was sent to parents who had not returned the reply card, 7 days after the mailing. All parents that indicated considering participation in the study received detailed written information (with an informed consent form) from the researchers (stage 2). After seven days a reminder was sent to all parents who had not returned the informed consent form. Subsequently, all parents who had not responded to the reminder were approached by telephone. Parents of children who returned a signed informed consent form were included in ARCADE.

**Figure 1 F1:**
[figure not shown]
**Flowchart of children in the study**. IC: Informed consent GP: General practitioner.

### Validation and updating of asthma prediction rule

#### Sample size calculation

The final prediction rule will contain up to 5–10 variables, taking into account practical efficiency. A widely accepted rule is that for each variable about 10 cases are required to prevent over-fitting of the model (Events Per Variable rule) [26]. This implies that 100 cases of asthma are needed to model these 10 variables. We expect the prevalence of asthma in the ARCADE cohort to be about 15%. With the inclusion of 771 children in the study, we may screen 11 variables. This prediction rule will be validated with the existing one of Eysink et al., as is recommended in the pertinent literature [24].

#### Measurements (Additional file 1)

##### Questionnaire background & symptoms

The parents of the children, annually, receive a questionnaire on (changes in) housing conditions, family history of allergy, asthma and eczema, presence of pets, breastfeeding, and asthma-related symptoms until the children reach the age of 6. Information about wheezing, rhinitis, eczema, cough, and phlegm is obtained by the Core Questionnaire of the International Study of Asthma and Allergy in Children (ISAAC) [27].

##### Allergy

Total immunoglobulin E (total IgE) and specific immunoglobulin E (specific IgE) directed against house dust mite, cat and dog dander is determined by radioallergosorbent test (RAST) at baseline [22,28]. Children under 4 who tested negative at baseline will be retested at the age of 4, to assess the predictive value of sero-conversion. A convenient method (finger prick) for sampling blood for analyses of total and specific IgE is used [28].

IgE positivity to house dust mite, cat and/or dog dander is defined as > 0.35 kU/l.

##### Inflammatory markers

Fractional Exhaled Nitric Oxide (FENO) is measured in the hospital or general practice at age 5 using an offline technique. Exhaled air is collected in a NO-impermeable Mylar balloon (ABC balloons, Zeist, The Netherlands). All balloons are analyzed in a NO-analyzer (Aerocrine AB; Sweden) within a time period of 6–8 hours after taking the samples [29].

##### Spirometry at age 5

Peak expiratory flow (PEF) is measured twice daily over a period of 14 days at age 5. PEF is performed on a One Flow FVC Memo (Clement Clark International, Essex, United Kingdom) by the children in their home environment, after a personal demonstration by a research assistant. The One Flow FVC Memo measures and stores the PEF automatically. Thus, errors due to incorrect reading and registration are prevented [30].

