### Discussion

The ARCADE study started two years ago and is an ongoing multicenter, prospective cohort study in which a prediction rule for 1 to 5 year old children at risk for developing asthma will be constructed. Also, the effects of frequently used 'real-world' treatment strategies on asthma severity in young children will be estimated.

Children were eligible for ARCADE if they were at risk of developing asthma; i.e. they visited their GP with complaints of coughing, wheezing and/or shortness of breath. We were able to select 1,938 children from the electronic medical records of the GPs and recruited 40% of those identified as at risk. Participation rates increased with the number of respiratory symptoms in the previous year. In the coming years all children will be followed until the age of 6.

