### Choices of methods in our study

#### Validation and updating of asthma prediction rule

For the construction of the prediction rule we collect data easy to obtain in general practice. Therefore we chose demographic data, data with respect to clinical history and additional tests that can easily be performed in general practice; i.e. total and specific IgE, FENO, and PEF. Measuring FENO using an offline technique is time consuming and expensive [29] however currently FENO can be measured with the 'NIOX mino' [54] , a small device that provides quick and easy FENO data. Other additional tests that could be performed in young children are the interrupter technique (Rint) and exhaled breath condensate (EBC). Although, the (additional) value of these tests is at present studied on a large scale, these measurements cannot be performed in general practice and were therefore not included in our study.

Several studies have postulated that early use of inhaled corticosteroids could prevent the onset of asthma and suggest over-treatment at a young age since inhaled corticosteroids appears to be effective in reducing symptoms in high-risk young children with frequent wheezing [17-20]. However, recent large RCT studies of Bisgaard et al. [55] and Guilbert et al. [56] showed that it seemed unlikely that early treatment prevents asthma. Therefore, we determined not to include the use of asthma medication such as β_2 _agonists and inhaled corticosteroids during the study period as a variable in our prediction rule.

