## Conclusion

The ARCADE study is an ongoing multicenter, prospective cohort study in which an existing prediction rule for 1 to 5 year old children at risk of developing asthma, will be validated and updated when needed. Also, the effect of different treatment strategies in young pre-school children, carried out by the GP, will be compared. This will provide more insight in treatment of asthma in young children since available literature on treatment of asthma in pre-school children precludes detailed treatment recommendations.

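### FENO and PEF, measured only at age 5, are planned inputs to a rule for children aged 1 to 5; if either is retained, the updated rule cannot be computed when a younger child presents

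*Protocol article*

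**What the plan says.** **Target.** The Discussion says that "a prediction rule for 1 to 5 year old children at risk for developing asthma will be constructed". The Conclusion gives the same age range for the rule to be validated and, where needed, updated: "an existing prediction rule for 1 to 5 year old children at risk of developing asthma".

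**Inputs.** The Abstract (Design) introduces specific IgE, FENO and PEF with the words "For our prediction rule, demographic data, data with respect to clinical history and additional tests". The Discussion section on validation and updating of the rule says that the data chosen for its construction include "additional tests that can easily be performed in general practice; i.e. total and specific IgE, FENO, and PEF".

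**Timing.** IgE "is determined by radioallergosorbent test (RAST) at baseline" (Allergy). For FENO: "Fractional Exhaled Nitric Oxide (FENO) is measured in the hospital or general practice at age 5 using an offline technique" (Inflammatory markers). For PEF: "Peak expiratory flow (PEF) is measured twice daily over a period of 14 days at age 5" (Spirometry at age 5). The outcome is asthma at age 6.

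**Model.** The statistical analysis section for the prediction rule describes a lasso-penalised logistic regression, a bootstrapped final model, and one easy-to-use rule derived from its coefficients. It names no moment at which the prediction is made.

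**The concern.** A prediction rule may use only what is known when the prediction is made. The Background justifies the study by early identification of high-risk children, and one of the existing rule's predictors is the child's age at presentation. The natural prediction moment is therefore when a child of 1 to 5 years comes to the GP. FENO and PEF do not exist in this study at that moment, except for children who enter at about age 5.

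Two things are at stake for the updated rule:

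- **Usability.** A score that contains an age-5 measurement cannot be worked out for a 2-year-old. The study collects no FENO or PEF at younger ages from which a coefficient for presentation could be estimated.
- **Meaning of the AUC.** The outcome definition looks back 12 months from age 6. A test at age 5 borders on that window or falls inside it. The AUC of a model that contains it describes prediction from age 5, and is not directly comparable with that of the existing rule, which uses neither test.

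**Working it through.** **1. The plan's own figure.** Inputs from the sample size section: 771 children, expected prevalence 15%, 10 cases per variable.

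- Expected cases: 771 × 0.15 = 115.65.
- Candidate variables: 115.65 / 10 = 11.57, rounded down to 11. This agrees with the article.

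**2. Children who entered before age 5.** Table 1 gives the ages at onset of enrolled children: 267 aged 1, 220 aged 2, 127 aged 3, 121 aged 4 and 36 aged 5, total 771. Treating these as ages at entry is an assumption.

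- Under 5: 267 + 220 + 127 + 121 = 735; 735 / 771 = 95.3%.
- Aged 5: 36 / 771 = 4.7%.
- At least about three years before the tests (ages 1 and 2): 487 / 771 = 63.2%.
- Mean lag to age 5 in whole years: (4 × 267 + 3 × 220 + 2 × 127 + 1 × 121) / 771 = 2103 / 771 = 2.7 years.

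Sensitivity: if every child entered one year older than the Table 1 age, those still under 5 would be 267 + 220 + 127 = 614, or 614 / 771 = 79.6%. The conclusion does not depend on which figure is used.

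**3. Possible difference in AUC.** The documents give no figure, so this is an illustration only. Assume independent, equal-variance binormal markers:

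- AUC = Φ(√(d0² + (r·d5)²) / √2), with each d = √2 · Φ⁻¹(AUC of that part alone).
- d0 stands for the other predictors (AUC 0.75 to 0.80 assumed) and d5 for the age-5 marker (AUC 0.60 to 0.70 assumed).
- r is the share of the marker's age-5 signal already present at presentation; r = 1 gives the model with the age-5 value.

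| Other predictors | Marker at age 5 | AUC, r = 1 | AUC at presentation | Difference |
|---|---|---|---|---|
| 0.75 | 0.70 | 0.804 | 0.750 (r = 0) | 0.054 |
| 0.75 | 0.70 | 0.804 | 0.779 (r = 0.7) | 0.025 |
| 0.80 | 0.60 | 0.810 | 0.805 (r = 0.7) | 0.005 |

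Over r from 0 to 0.7 the difference runs from about 0.005 to 0.054. It is zero if the marker is fully stable from presentation to age 5, or if it is not retained.

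**4. Do the planned safeguards help?** Shrinkage and bootstrapping address overfitting to the sample. They resample the same age-5 values and so reproduce the same timing. The lasso selects on association with the outcome and cannot reject a predictor because it is unavailable at presentation.

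**5. Effect of the fix on sample size.** Dropping FENO and PEF from the primary candidate set leaves 115.65 expected cases and 11 variables.

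**The case against.** The strongest reply is that FENO and PEF are only candidates. The lasso was chosen partly because it can set coefficients to zero, and if both drop out nothing is lost. This stands: the harm is conditional on retention. It is also a reason to settle the candidate set before fitting.

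A rule that keeps these tests could still be applied at age 5, inside the stated age range. True, but only 4.7% of enrolled children entered at that age.

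The article is condensed, and a fuller plan might hold separate baseline and age-5 models. That cannot be excluded. The point, however, rests on what the article states: the tests are chosen for constructing the rule, the rule is for children from age 1, and one final model and one rule are described.

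A reader might infer more than the text supports in four respects:

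- **That sero-conversion is also an input.** The Allergy section says only: "Children under 4 who tested negative at baseline will be retested at the age of 4, to assess the predictive value of sero-conversion". The article's lists of tests for the rule do not name sero-conversion, and a separate analysis fits that sentence equally well.
- **That accuracy is inflated.** The article neither shows nor quantifies this. It requires both retention and a marker that is more informative near age 6 than at presentation.
- **That cross-validation of the existing rule is compromised.** It is not. That rule uses age at presentation, wheeze, family history of pollen allergy and specific IgE, and IgE is taken at baseline.
- **That needing follow-up to age 5 selects the sample further.** A child with an outcome at age 6 was already followed at 5. The extra loss is non-performance among the 131 invited: 17 (13.0%) for FENO and 14 (10.7%) for PEF.

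**Conclusion.** The point holds for the updated or newly constructed rule. Two tests measured only at age 5 are named as inputs to a rule for children from age 1, and no stated prediction time reconciles this. If either test is retained, the rule cannot be computed at presentation for about 95% of a cohort like this one (735 of 771, taking Table 1 ages as entry ages; 79.6% if all entered a year older). Its AUC would then describe prediction from about one year before the outcome. Whether that AUC is higher than the one attainable at presentation, and by how much, cannot be read from the article; the 0.005 to 0.054 range rests wholly on assumed inputs. The event count, the 11 candidate variables and the cross-validation of the existing rule are not in question.

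**What to change.** Before any model is fitted:

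1. State presentation (study entry) as the prediction time point of the primary updated rule.
2. Restrict its candidate predictors to what is known then: demographics, clinical history, and baseline total and specific IgE.
3. Analyse FENO and PEF in a separate landmark model that starts at age 5 and includes the children under follow-up at that age. Report their added value over the baseline linear predictor. If sero-conversion is modelled, treat it in the same way from age 4.
4. Report the AUC of each landmark model as its own, and do not attribute it to the presentation rule or set it directly against the existing rule.

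The cost is a change of analysis wording and one or two additional models on data already being collected. The small downside is that the presentation rule may show a lower AUC than a model that mixes entry and age-5 data.

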#### Outcome (asthma at age 6)

Asthma is defined as a combination of current symptoms (complaints of wheezing and/or shortness of breath and/or recurrent coughing) and/or use of asthma medication (β_2 _agonists and/or inhaled corticosteroids) during the previous 12 months in combination with airway hyperresponsiveness to methacholine. Airway hyperresponsiveness is defined as PC_20 _FEV_1 _≤ 8.0 mg/ml, or > 10% increase in FEV_1 _after rapid acting beta-2-agonists (salbutamol) inhalation if baseline airflow obstruction precluded a methacholine challenge [31].

Spirometry is obtained using a Pulmoassist 2 spirometer (Jaeger, Würzburg, Germany). Bronchial responsiveness to increasing doses of methacholine (PC_20_) is measured with a gauged DeVilbiss 646 nebulizer (DeVilbiss, Somerset, MA, USA) with an output of 0.13 ml/min according to the modified method of Cockroft et al. [32]. Children on asthma-medication will withheld all bronchodilators 48 hours before the test. In case of shortness of breath children receive ongoing rapid acting beta-2-agonists up to 8 hours before the test.

